### Exclusion criteria

We will exclude stroke patients with any one of the following clinical conditions from the medical screening process: (1) bleeding disorders, (2) procedures or surgeries for peripheral vascular diseases, (3) psychiatric disorders, (4) severe diseases in the lower urinary tract, (5) acute or chronic infectious diseases in the lower urinary tract, or (6) pregnancy (laboratory results from urinalysis). In addition, patients (7) whose medications for UR or relevant symptoms (urinary incontinence drugs or diuretics) have been changed within 3 days or (8) for whom onset of treatment is within 1 week prior to the study, along with those with a Glasgow Coma Scale score of <8 points, will be excluded. Finally, we will also exclude those who have fears about acupuncture therapy.

### Dropout criteria

Patients will be removed from the study if they are unwilling to continue their participation in the study. Patients who fail or anticipate to fail in continuing at least seven sessions will be dropped from the study, too.

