**Methods/design:**

A multicenter, blinded, randomized controlled trial will be conducted in three hospitals in the Republic of Korea. We are recruiting 54 stroke survivors (aged >19 years), who were diagnosed with urinary retention based on the results of two consecutive post-void residual (PVR) tests, and dividing them randomly into two arms: the EA and Park-sham control groups.

They will receive ten sessions of EA or sham treatment for 2 weeks. The participants will be blinded with non-penetrating needles and fake sounds of EA stimulators. The daily PVR ratio will be primarily measured at baseline and at the end of the study to statistically test the effectiveness of EA for poststroke urinary retention. Then, the Korean version of the Qualiveen Questionnaire, the Korean version of the International Prostate Symptom Score, and the blinding index will be assessed. After each EA session or sham EA, adverse events will be reported to evaluate the safety of EA.

Results will be analyzed by using the independent *t*-test or Mann-Whitney *U* test, based on both intention-to-treat and per-protocol principles.

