### Blinding

The patients and outcome assessors will remain blinded during the study. Patients assigned to the sham group will undergo a similar treatment as those assigned to the EA group. Because we will use the Park-sham with non-penetrating acupuncture needles as control, electrostimulation will be turned on without conductance. In addition, we will use the same guide tubes used in the Park-sham acupuncture needles in the intervention group, too. Aside from the practitioners who will administer the EA or sham treatment, there will be an independent outcome assessor who will not be notified about the patients’ allocated arms.

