### Primary outcome

To evaluate the effectiveness of EA treatment over the sham device for poststroke UR, we will primarily assess the change in daily PVR urine ratios between the baseline and end point of the last session. The daily PVR ratio is computed by dividing the daily PVR urine volume by the daily PVR urine volume plus spontaneous voiding volume. The daily PVR urine volume for 24 hours will be examined with ultrasonography scanning. If the PVR urine volume is more than 100 mL, the residual will be removed through intermittent cauterization before the scanning. When spontaneous urination is impossible, a 24-hour weight change in diaper will be measured for the self-voiding volume.

If the urinary tract is infected at the end, the outcome assessor will measure the PVR urine volume on the third day of the last session after anti-UTI treatment for 48 hours. Otherwise, PVR urine volume will be measured on the next day of the last session.

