### Data analysis

We will analyze results primarily based on the principle of intention - to - treat (ITT) and subordinately based on the per - protocol (PP) principle. The ITT analysis will include any participants who are randomly allocated and have at least one EA or sham session. Missing values will be imputed by the last observation carried forward. The PP analysis will cover only the patients who have at least seven sessions of EA or sham treatments and have no medical diagnosis of UTI at the end point.

Continuous variables will be tested by the independent *t*-test if normality is obtained. Otherwise, the Mann-Whitney *U* test will be implemented. The categorical variables will be analyzed by the Pearson *χ*^2^ test or Fisher's exact test.

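### The seven-session dropout rule removes patients from the study whom the primary ITT analysis must include, leaving them with a carried-forward change of zero

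*Protocol article*

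**What the plan says.** Four parts of the protocol article bear on this.

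- **Dropout criteria.** After listing patients unwilling to continue, the section adds: "Patients who fail or anticipate to fail in continuing at least seven sessions will be dropped from the study, too".
- **Data analysis.** ITT is primary: "The ITT analysis will include any participants who are randomly allocated and have at least one EA or sham session". Per-protocol is subordinate and uses the same threshold: "The PP analysis will cover only the patients who have at least seven sessions of EA or sham treatments", with absence of UTI at the end point as a further condition. For gaps: "Missing values will be imputed by the last observation carried forward".
- **Abstract and Primary outcome.** The course is ten sessions in two weeks. On the outcome: "The daily PVR ratio will be primarily measured at baseline and at the end of the study". Apart from the UTI case, which is measured on the third day, the timing hangs on the last session: "Otherwise, PVR urine volume will be measured on the next day of the last session".
- **Blinding.** Patients and outcome assessors are stated to be blinded. The assessor is separate from those who treat: "Aside from the practitioners who will administer the EA or sham treatment, there will be an independent outcome assessor". Practitioners are not among those stated to be blinded.

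**The concern.** Receiving too little treatment is handled as leaving the study. An adherence threshold belongs in the definition of the per-protocol set, where the article already has it. Used as a dropout rule, it also decides who stays under observation, and it does so for patients who may be quite willing to be measured, since unwillingness is a separate ground.

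At stake is the primary estimate. Patients with one to six sessions count in the ITT comparison, but with a filled-in value instead of an outcome. If the arms lose similar numbers, the treatment difference shrinks. If they lose different numbers while both improve, a difference can appear where none exists. No later analysis can recover outcomes that were not collected. The ground of expected failure adds a judgement for which the article gives no criterion and no decision-maker.

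**Working it through.** **1. The passages side by side**

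| Sessions received | Dropout criteria | Primary ITT set | Per-protocol set |
|---|---|---|---|
| 0 | dropped | out | out |
| 1 to 6 | dropped | in | out |
| 7 to 10 | stays, unless expected to fall short or unwilling | in | in, if no UTI at the end point |

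The conflict is the middle row. For these patients the only PVR ratio certain to exist is the baseline one. Carrying it forward gives change = baseline − baseline = 0. The same holds for a percentage change, the scale named under Sample size.

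**2. The plan's own figure**

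Sample size gives 42 evaluable patients (21 per arm), alpha 0.05, power 0.80 and a 20% drop rate. 21 / (1 − 0.20) = 26.25, rounded up to 27 per arm, 54 in total. This reproduces. The 42 itself cannot be rebuilt, because neither effect nor SD is given. Solving back for 21 per arm (two-sided t-test; sidedness is not stated, so this is an assumption) gives a standardised difference of 0.886.

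**3. How many patients**

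0.20 × 54 = 10.8, about 11 (by the rounded figures, 54 − 42 = 12). The 20% is an overall rate that also covers patients unwilling to continue, so about 11 is a ceiling for the seven-session rule.

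**4. Equal dropout: power**

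Assume SD of change 1, control improvement m, EA improvement m + 0.886, and a fraction q = 0.20 of each arm set to zero, independently of outcome.

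- Arm mean = (1 − q) × mean.
- Arm variance = (1 − q)(1 + mean²) − [(1 − q) × mean]².
- Difference in means = 0.8 × 0.886 = 0.709 for any m.

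| m (SD) | Variances, control / EA | Effective standardised difference | Power, 27 per arm |
|---|---|---|---|
| 0 | 0.80 / 0.93 | 0.76 | about 79% |
| 0.5 | 0.84 / 1.11 | 0.72 | about 74% |
| 1 | 0.96 / 1.37 | 0.66 | about 66% |

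If all 27 per arm are measured and the full 0.886 holds, power is about 89%. That is an upper bound, because under-treated patients may respond less. With 10% zero-filled, power is about 84% (m = 0) or 82% (m = 0.5).

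**5. Unequal dropout: type I error**

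Let both arms truly improve by the same m, with fractions q1 and q2 zero-filled. The false difference is (q2 − q1) × m. At 10% vs 30% this is 0.20 × m: 0.05, 0.10 or 0.20 SD for m = 0.25, 0.5 or 1. Simulated t-tests with 27 per arm give:

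| Dropout split | m = 0.25 | m = 0.5 | m = 1 |
|---|---|---|---|
| 20% vs 20% | about 5% | about 5% | about 5% |
| 15% vs 25% | about 5% | about 6% | about 7% |
| 10% vs 30% | about 6% | about 7% | about 12% |

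Steps 4 and 5 treat every dropout as zero-filled, so they show the joint effect of the dropout rule and the carry-forward, at the ceiling.

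**The case against.** Five objections deserve weight.

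- **The end-point visit may not be skipped.** The article never says that it is, and the ITT definition expressly admits patients with one session. This stands as a caution: loss of the measurement is inferred from removal from the study, from timing tied to the last session, and from reliance on carry-forward. Nothing in the text provides for the measurement, however, so the inference is the natural one.
- **About 11 patients overstates the loss.** Accepted. It is a ceiling, and some of those patients would withdraw consent and remain unmeasured under any fix.
- **A reader might infer that the trial will run at 12% type I error.** The documents do not support this. That figure needs a threefold imbalance in dropout and a 1 SD improvement in both arms. Such a sham-arm improvement exceeds the whole between-arm difference (0.886 SD) implied by the sample size. The article gives no SD and no expected imbalance. With equal dropout there is no inflation.
- **A reader might infer that practitioners will remove patients according to arm.** The article does not say this either. It names no one as making the forecast, and as worded the patients themselves, who are blinded, may be the ones anticipating failure. Removal that depends on arm is possible, not shown.
- **Requiring one session is an openly stated modified ITT definition.** True, and it is separate from the seven-session conflict. It is only a secondary point here.

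The contradiction between Dropout criteria and Data analysis survives all five.

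**Conclusion.** The point holds in this form: the dropout rule takes out of the study patients whom the primary analysis keeps in, and under the stated carry-forward they can contribute only a change of zero unless an end-point measurement is made that the article does not provide for. This is stated conduct, not detail left to an analysis plan.

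The likelier damage is dilution. With 20% zero-filled in each arm, power falls to between about 79% and 66%, depending on how much control patients improve, against at most about 89% with complete measurement. The 20% allowance therefore need not protect the planned 80%: the inflation in the sample size assumes that dropouts leave the analysis, whereas here they stay in it as zeros. A false-positive risk above 5% needs both unequal dropout and improvement in both arms; over the cells examined it runs from about 5% to 12%.

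Confidence is high on the textual conflict. The sizes rest on a back-solved effect and on assumed mean changes and dropout splits, and the true number affected is unknown.

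**What to change.** Amend Dropout criteria and Data analysis so that:

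1. receiving fewer than seven sessions affects per-protocol membership only;
2. expected failure to reach seven sessions is deleted as a ground for leaving the study;
3. unless consent is withdrawn, the end-point outcomes (PVR ratio, K-QQ, K-IPSS and urinary diary) are measured in every randomised patient. Patients who stop early need a fixed end-point day counted from randomisation or first session, for example the day after the scheduled tenth session, because the present timing follows the last session and gives them no comparable day;
4. as a secondary point, all randomised patients are analysed in their allocated arm, including those with no session.

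The rules on when treatment stops are not touched. The cost is a short amendment and keeping end-point assessments for at most about 11 patients; these assessments were already planned for each recruited patient. The sample size stays at 54.

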### Randomization

Random sequences were generated separately in each site with the R package (R Foundation for Statistical Computing, Vienna, Austria, https://www.r-project.org) to allocate participants into either the EA or sham group. The allocation ratio was 1:1. From each center, at least 14 participants will be recruited, and the last 12 persons will be competitively enrolled among all the three sites. Only the delegated sub-investigators can access the security electronic file of the randomization table and assign the participants. Practitioners from each site will call or send a message to the sub-investigators in order to allocate the participants in their own hospitals. After assignments are completed, a sub-investigator from the primary site, Kyung Hee University Korean Medicine Hospital, will allocate the 12 participants from the three sites to the last participant. The investigators, who will generate the random number and assignments, will be blinded to the arm where each participant will be allocated.

### Blinding

The patients and outcome assessors will remain blinded during the study. Patients assigned to the sham group will undergo a similar treatment as those assigned to the EA group. Because we will use the Park-sham with non-penetrating acupuncture needles as control, electrostimulation will be turned on without conductance. In addition, we will use the same guide tubes used in the Park-sham acupuncture needles in the intervention group, too. Aside from the practitioners who will administer the EA or sham treatment, there will be an independent outcome assessor who will not be notified about the patients’ allocated arms.

### Interventions

The EA and sham EA regimens are based on traditional Korean medicine. We referred to the textbook [14] and consulted acupuncture and stroke specialists.

The participants allocated to the EA group will receive five sessions per week of EA therapy for 2 weeks (ten sessions in total). After inserting needles (stainless steel, 0.25 mm in diameter and 4.0 mm in length; Dong Bang Acupuncture Inc., Republic of Korea) using the Park-sham guide tube on bilateral acupoints BL31, BL32, BL33, and BL34 (eight points in total) at 5–10 mm in depth, the *de qi* sensation is elicited. The locations of the acupoints according to the World Health Organization Standard Acupuncture Point Locations in the Western Pacific Region are illustrated in Fig. 2 [15]. *De qi* means an acupuncture needle sensation of soreness, tingling, fullness, ache, coolness, warmth, and heaviness, and a radiating sensation at and around the acupoints to the point of a threshold that elicits nerve impulse transmission to the cerebral cortex [16]. Then, electrostimulation will be administered for 20 minutes at a moderate frequency of 30 Hz (STN-111, Stratek, Republic of Korea).

**Fig. 2 Fig2:**
[figure not shown]
The locations of acupoints BL31, BL32, BL33, and BL34. In the sacral region, BL31, BL32, BL33, and BL34 are located in the first, second, third, and fourth posterior sacral foramens, respectively. (World Health Organization Standard Acupuncture Point Locations in the Western Pacific Region)

We will use the Park-sham device in the control group. The non-penetrating needles of the sham acupuncture will be implemented on the same eight bilateral acupoints. The total number of sessions of sham EA is ten (five times per week for 2 weeks). The electrostimulation will also be administered for 20 minutes at moderate frequency (30 Hz; STN-111, Stratek, Republic of Korea), even though the stimulation will not be delivered through the skin because of the non-penetrating needle of sham device.

The use of conventional therapies will be allowed during the study for both groups. The conventional therapies consist of general supportive care, preventive or therapeutic management for medical/neurological complications, or drug treatments with antiplatelet agents, anticoagulants, or neuroprotectants. Moreover, stroke management with traditional herbal medications, acupuncture without electrostimulation, or rehabilitation for stroke complications will be permitted during the trial. However, any drugs, herbal medications, or rehabilitation that could affect UR will be prohibited. The study will conform to clinical practice guidelines for stroke management in Korea [17].

Practitioners who have over 1 year of clinical experience will perform the EA or sham EA treatments.

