## Discussion

This randomized controlled trial aims to determine whether EA treatment is effective for UR in poststroke survivors. The effectiveness is represented by the relative proportion of urine residuals and voiding volumes. Because this study is designed to provide clinical evidence for the relevant patients and practitioners, we have chosen not to eliminate any other general treatments for poststroke survivors.

The eight acupoints were identified based on the guideline published by the World Health Organization. In the sacral region, BL31, BL32, BL33, and BL34 are located in the first, second, third, and fourth posterior sacral foramens, respectively [15]. In the literature on traditional Korean medicine, these points have been reported to possibly have the property to recover bladder dysfunction, and they have shown clinical effectiveness for poststroke detrusor overactivity in a previous study [11]. The acupoints are considered to have a possible mechanism that the acupuncture stimulation directly increases the excitability of the pelvic nerve, which consequently innervates the detrusor muscle [2].

Park-sham acupuncture is a placebo acupuncture device invented to stabilize the needle in position with an additional guide tube preventing skin penetration [29]. This sham device was validated to be inactive and indistinguishable [30]. We have decided to use the same guide tubes as Park-sham acupuncture to prevent participants from discovering the group to which they belong. The apparatus for electrostimulation will be activated in the sham control group to make the participants hear the same machine sound so as to let them believe they are under real acupuncture treatment. Because Park-sham acupuncture does not intrude the skin, electrostimulation will not be conducted through the body. Success or failure of these blinding strategies will be appraised at the end of the study by the BI [26].

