Bladder dysfunction, including UR, poses an obstacle for rehabilitation and QoL improvement in poststroke patients [2, 4–6]. Catheterization, the major therapeutic approach, confers the risk of UTI [2]. A preliminary clinical study showed the potential benefits and safety of EA treatment for stroke patients with UR [2]. However, the study was performed only with a single group and lacked the methodological requirements and statistical power to establish the evidence for treatment. Overall, clinical trials of EA for any urinary dysfunction, with a placebo control, are rare, except for the study of poststroke detrusor overactivity [11]. We targeted UR in poststroke patients and designed a randomized, sham-controlled trial to be conducted in multiple sites to appropriately generalize the results of the trial, following the CONSORT [12] and STRICTA guidelines [13].

At the end of the project, we expect that the findings will provide clinical evidence of the effectiveness of EA treatment for improving UR in stroke survivors.

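### The ban on co-treatments that could affect urinary retention leaves out acupuncture, so manual needling at the trial's own points (BL31–BL34) is allowed in both arms

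*Protocol article*

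**What the plan says.** The co-treatment rule is in the protocol article under Methods/design, Interventions (the paragraph after Fig. 2). Conventional therapy is allowed in both groups. For stroke management, the paragraph says that traditional herbal medication, "acupuncture without electrostimulation, or rehabilitation for stroke complications will be permitted during the trial". The next sentence sets the limit: "However, any drugs, herbal medications, or rehabilitation that could affect UR will be prohibited".

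The same section places EA and sham at the same eight bilateral points, BL31 to BL34. In the sham arm, "the stimulation will not be delivered through the skin because of the non-penetrating needle of sham device". In the EA arm, needling first elicits de qi, described as a sensation reaching "to the point of a threshold that elicits nerve impulse transmission to the cerebral cortex". Current is applied only after that.

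The Discussion gives the reason for the points. In the traditional Korean medicine literature, "these points have been reported to possibly have the property to recover bladder dysfunction", and the proposed mechanism is that "the acupuncture stimulation directly increases the excitability of the pelvic nerve". It also states the general policy on other care: "we have chosen not to eliminate any other general treatments for poststroke survivors".

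**The concern.** The permission names three modalities: herbal medication, acupuncture and rehabilitation. The ban repeats the first and third, adds drugs, and omits acupuncture, which is the modality closest to the test treatment. As written, manual needling at BL31–BL34 given as stroke management complies with the plan in either arm. Needling for urinary symptoms is not clearly excluded either, if urinary retention is read as a stroke complication.

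What is at stake is the contrast in the primary outcome, the change in daily post-void residual (PVR) ratio. The sham is built to deliver nothing through the skin at these points. If some sham patients have real needles placed there, and if that helps them more than it helps patients already receiving EA at the same points, the EA–sham difference shrinks.

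**Working it through.** **1. The text.** The two adjacent sentences compare as follows.

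| Modality | Permitted as stroke management | Barred if it could affect urinary retention |
|---|---|---|
| Herbal medication | yes | yes |
| Acupuncture without current | yes | not named |
| Rehabilitation | yes | yes |
| Drugs | yes (stroke drugs, listed in the preceding sentence) | yes |

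No other section limits co-treatment acupuncture by point, depth, purpose or frequency.

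**2. Whether manual needling there could meet the authors' own test.** The Discussion attributes a possible bladder effect to the points and words the mechanism as acupuncture stimulation, without naming current. The EA procedure elicits de qi before current starts. This makes an effect plausible, not established: the two numbered sources for a bladder effect at these points, references 2 and 11, are described in the Background and Discussion as EA studies (for reference 2: "A preliminary clinical study showed the potential benefits and safety of EA treatment for stroke patients with UR").

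**3. The plan's sample size.** The Sample size section gives 42 in total, 80% power, a 0.05 level and 20% dropout. 42/2 = 21 per arm, and 21/(1 − 0.20) = 26.25, which rounds up to 27 per arm, or 54. This matches the plan. The 42 itself cannot be rebuilt, because no between-group difference or SD is given. Taking a two-sided t-test (an assumption, since sidedness is not stated), 21 per arm and 80% power imply a difference of d = 0.886 SD.

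**4. Illustration of dilution.** Three inputs are assumed; none comes from the document:
- f: the share of patients in each arm given manual needling that acts on retention
- r: its effect as a fraction of the EA effect
- a: the part of that effect that adds on top of EA

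With EA effect d, needling raises the sham mean by f·r·d and the EA mean by f·r·a·d. The contrast is then d × (1 − f·r·(1 − a)).

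| f | r | a | Contrast (SD) | Power, 21 per arm | Power, 27 per arm |
|---|---|---|---|---|---|
| any | any | 1 | 0.886 | 80.0% | 89.2% |
| 0.1 | 0.25 | 0 | 0.886 × 0.975 = 0.864 | 78.0% | 87.6% |
| 0.1 | 0.5 | 0 | 0.886 × 0.95 = 0.842 | 75.9% | 85.9% |
| 0.3 | 0.5 | 0.5 | 0.886 × 0.925 = 0.820 | 73.6% | 84.0% |
| 0.3 | 0.5 | 0 | 0.886 × 0.85 = 0.753 | 66.3% | 77.5% |

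The first row also covers no needling at all. The 27-per-arm column is the most the intention-to-treat set could hold. It is an upper bound, since values carried forward from dropouts may dilute the effect. At 27 per arm, power stays at or above 80% until the contrast falls to 0.777 SD, a shrinkage of 12.3%.

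**The case against.** The case on the other side has four parts.

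- **Condensed article.** A list of barred points is operational detail that the full protocol may hold. That is fair as regards the list. But the article states the ban itself as an explicit list of modalities, and acupuncture is missing from it.
- **Limited purpose.** Acupuncture is allowed only as stroke management, and the document mentions no use of these sacral points other than for the bladder. Needling aimed at retention is arguably outside the intent. This carries some weight, but herbal medication and rehabilitation sit under the same framing and were still named in the ban. The framing also limits the purpose of needling, not the points used.
- **Thin evidence and no size.** The support for a manual-needling effect is traditional literature and a mechanism cited to an EA study, and f, r and a are all invented. This stands. The power figures show what could happen and are not estimates. Nothing in the document supports 30% use at these exact points.
- **Deliberate pragmatism and safe direction.** The authors chose to leave general care in place, and any effect would work against EA. Both points are true. But the authors already bar other modalities that could affect retention, so adding acupuncture completes their own rule. Balance between arms prevents bias towards EA; it does not prevent dilution when the effects are not additive.

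**Conclusion.** The point holds as a gap in wording. The stated rule lets patients in either arm receive manual needles at the trial's own points, including sham patients at the sites where the sham is meant to be inert.

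The likely consequence is some loss of contrast and power, not a false positive in favour of EA. It is nil if use is equal between arms and the effects add. At low assumed use (f = 0.1, r up to 0.5) the loss runs from 0 to about 4 points at 21 per arm, and from 0 to about 3 points at 27. The less favourable case of f = 0.3, r = 0.5, a = 0 brings power to 66% and 77.5%.

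All of these rest on assumed f, r and a, and on a back-solved 0.886 SD under a two-sided t-test. The document does not say how often such needling would occur. The finding is minor: worth correcting because correction is cheap, and no threat to the trial's validity.

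**What to change.** Add acupuncture to the modalities barred when they could affect urinary retention, in both arms. Because that phrase is vague for needling, state the minimum it covers: any needling at BL31–BL34, and any needling given for urinary symptoms. Acupuncture for other stroke complications stays permitted, so the choice to leave general poststroke care in place is kept.

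The cost is one added word, a short list of points, and telling the sites. Patients lose a small part of optional acupuncture for 2 weeks. No extra staff or visits are needed, and the sample size stays at 42 calculated and 54 recruited.
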